#### Sample size

A sample size of 480 couples, 120 per each of the four study arms, was chosen to ensure sufficient statistical power to detect meaningful differences in our primary outcomes of couple-level ART/PrEP initiation and adherence between intervention and control groups. These power calculations assume 80% power, and an intraclass correlation coefficient (ICC) of 0.05 (based on the team’s previous R01 study with couples in Cape Town) [22], with an estimated follow-up of 95% at 3-month follow-up and 90% at 6-month follow-up. On average, a sample size of 97 community members in each of the 24 catchment areas was calculated to detect a 10% difference between control and intervention conditions on measures of stigma reduction. Using a two-sided chi-square test of proportions with a significance level of 0.05 and nested design model with additivity on the primary intervention effect (stigma awareness community workshop as compared with no community workshop) and secondary intervention effect (CHC+ as compared with HTS), our sample size was selected to ensure power for contrasts based on the presence of an interaction between the community-based stigma awareness workshop and the CHC+. For a hypothesis related to ART/PrEP initiation among couples in the CHC+ arm as compared with couples in the HTS arm, we will be able to detect a minimal effect size of 0.23. The minimal effect size of the CHC+ intervention on ART/PrEP adherence by couples in the CHC+ arm at 6 months is estimated to be 0.34 compared with couples in clinics in the HTS arm. For the evaluation of the efficacy of the stigma awareness workshop plus the CHC+ as compared with no stigma awareness workshop plus HTS (control), the minimal effect size related to ART/PrEP initiation is estimated to be 0.45. For examination of the intervention components’ effects (stigma awareness workshop and the CHC+) on ART/PrEP adherence), the minimal effect size is estimated to be between 0.26 and 0.6 for retention at 3-month and 6-month follow-up.

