#### Data collection: Couples follow-up assessments

Follow-up assessments will be carried out with young couples at 3- and 6-month follow-up intervals to assess participants’ progress and collect relevant data. During these follow-up visits, participants will be requested to reconsent, update their contact information, and complete a follow-up questionnaire utilizing ACASI methodology. This ensures privacy, facilitates accurate responses, and allows for real-time error checking and interpretation assistance, as needed. Biological testing will be conducted to assess HIV status if the partciant was HIV negative at baseline, pregnancy, alcohol use, and other drug use. Participants who report being on and adhering to PrEP or ART will have DBS collected to measure drug concentrations, serving as an objective measure of medication adherence. Participants will be offered a referral to the clinic for ART or PrEP services, ensuring appropriate medical support and treatment. To support participants’ adherence to PrEP or ART regimens and address any concerns or questions that may arise, patient navigation will be provided. This involves regular phone calls and text messages to offer guidance, reinforce medication adherence, and provide ongoing support throughout the study period.

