#### Overall study measures

We aim to assess the impact of the stigma awareness workshop on the knowledge, attitudes, and behaviors of the community toward young women and men who are seeking or need health services. Community-level outcomes will be evaluated through repeated measures on their beliefs about people who use alcohol or other drugs, their knowledge about ART and PrEP, their attitudes, beliefs, and behaviors toward people living with HIV, challenges or support from the community to take HIV prevention, and where to go for needed health services and information.

At the couple level, our primary outcomes will include the initiation of ART/PrEP and the documentation of HIV status. We will measure ART/PrEP adherence, as well as PrEP concentration via medical records and dried blood spot (DBS) samples during follow-up appointments. Adherence will also be assessed through self-reported past 30-day use, refills, and the duration of ART or PrEP usage, documented medical records, and DBS. To evaluate substance use, we will conduct baseline and follow-up assessments using rapid urine-based drug screening. This method will detect metabolites of commonly used drugs, providing insight into recent AOD use. Furthermore, we will examine secondary couples-level outcomes, such as self-reports on the frequency of AOD use; experiences of GBV; sexual risk behaviors, including condomless sex; AOD use before sexual encounters; engagement in concurrent partnerships; involvement in sex trade; contraceptive use; and perceptions of HIV risk. We will also assess attitudes toward traditional gender roles, empowerment, assertiveness, and communication between partners regarding testing, status, or sexual relationships. Participants will be asked to self-report experiences of stigma in their communities. To measure these outcomes, we will use a revised risk behavioral assessment (RRBA) [39] that also includes ART/PrEP partner support, treatment readiness, social impact of ART/PrEP use, and health service access and utilization (see **Table 3**).

**Table 3 pone.0305056.t003:** Outcome measures for couples and communities.

Outcome	Measures	Time Points Revised
**Aim 2: Stigma awareness and education on community members’ attitudes and behaviors toward young women and men who use AODs and other people seeking HIV services (testing/ART/PrEP) and other health services.**		

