Increased communication between partners regarding testing, HIV, and STI/STD status; other partners; sexual negotiation; and condom use.	**Self-report:** Communication with partner about testing, HIV and STI/STD status, other partners, sexual negotiation and condom use as measured by the PRBA+.	Baseline, 3 months, and 6 months FU
**Aim 3: The Couples Health CoOp Plus proposes to increase both partners’ PrEP/ART initiation and adherence. fgAim 4: Examine the interaction of the stigma awareness workshops and Couples Health CoOp Plus intervention on increased PrEP and ART initiation, retention, and adherence for both partners.**		
FGEvidence of ART or PrEP initiation.	**Medical Record Review:** ART/PrEP initiation and HIV status as documented by medical record.	6 months FU
Increased biological evidence of ART or PrEP adherence.	**Biological:** ART adherence will be measured using viral load or cluster of differentiation 4 (CD4) count measures recorded in the participant’s medical record. Threshold for adherence will be cluster of differentiation 4 (CD4) count (more than 200) and HIV viral load (less than 50 copies per ml). Tenofovir Diphosphate (TFV-DP) and FTC Triphosphate (FTC-TP) concentrations in dried blood spots (DBS) with drug concentrations of greater than 700 femtomoles (fmol)/liters(L) will be considered adherent to PrEP.	6 months FU
Increased reporting ART or PrEP adherence.	**Self-report:** Past 30-day use, missed doses, time in weeks, and patterns of use of ART or PrEP as measured by the RRBA/PRBA+.	3 months, and 6 months FU
Increased evidence ART or PrEP adherence; Increased persistence and reduced discontinuation.	**Medical Record Review:** Refills, number of months on ART/PrEP since initiation, and follow-up visit attendance as recorded in clinic medical records.	6 months FU
**Note:** AOD, alcohol and other drugs; ART, antiretroviral therapy; ASSIST, Alcohol, Smoking and Substance Involvement Screening Test; GIS, Gender Ideology Scale; PRBA+, Pretoria Risk Behavior Assessment; PrEP, pre-exposure prophylaxis; RRBA, Revised Risk Behavior Assessment; SRH, sexual and reproductive health; STI/STD, sexually transmitted infection/disease.		

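### The dried-blood-spot measure of PrEP adherence has a cutoff whose unit is probably wrong and does not name its analyte, and samples are planned only for participants who report adhering

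*Protocol article*

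**What the plan says.** The Sample size section of the protocol article speaks of "our primary outcomes of couple-level ART/PrEP initiation and adherence between intervention and control groups", so adherence is treated there as a primary outcome.

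Table 3, under Overall study measures, gives the biological definition. For PrEP it names two analytes in DBS, TFV-DP and FTC-TP, and states that "drug concentrations of greater than 700 femtomoles (fmol)/liters(L) will be considered adherent to PrEP". It does not say whether one analyte governs, or whether either or both must pass. The row is scheduled at 6 months only.

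The section on couples' follow-up assessments, which covers the 3- and 6-month visits, says who is sampled: "Participants who report being on and adhering to PrEP or ART will have DBS collected to measure drug concentrations". It describes this as "serving as an objective measure of medication adherence". It does not define adhering.

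The text of Overall study measures sets no such condition. It plans to measure "PrEP concentration via medical records and dried blood spot (DBS) samples during follow-up appointments", and adds: "Adherence will also be assessed through self-reported past 30-day use, refills, and the duration of ART or PrEP usage, documented medical records, and DBS".

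The statistical analysis section takes the couple as the unit for adherence and plans analyses at both 3 and 6 months.

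**The concern.** There are two separate weaknesses in the same measure.

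- **The cutoff.** A threshold per litre of blood fits poorly with a dried spot, and in that unit the number is extremely small. With two analytes and no governing one, two analysts could also classify the same participant differently.
- **The sampling rule.** An objective measure is wanted because self-report may be wrong. If blood is taken only when the participant reports adhering, the measure can refute an over-reporter. It cannot find drug in someone who reports missed doses and so is not sampled. The report is made after randomisation, and CHC+ teaches adherence and has couples plan for it. The arms may therefore differ in who reports adherence, and hence in who is sampled, for reasons other than drug-taking.

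The two weaknesses compound. Sampling only self-declared adherers leaves DBS the single job of refuting over-reports, and too low a cutoff would weaken that job as well. An uncorrected cutoff can be mended later from stored results, but blood that was never collected cannot be recovered.

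**Working it through.** The article gives no derivation, assay limit, sample volume or expected concentration for the cutoff, so there is no figure to reproduce. The first check is unit arithmetic. The second is a simple classification model on assumed rates.

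**1. Size of the cutoff.** Input from Table 3: 700 fmol/L. Assumption: 1 to 50 microlitres of blood per sample.

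- Per microlitre: 700 / 1,000,000 = 0.0007 fmol.
- In 1, 3, 10 and 50 microlitres: 0.0007, 0.0021, 0.007 and 0.035 fmol.
- If 700 fmol was meant per sample of 1 microlitre: 700 / 0.000001 L = 700,000,000 fmol/L, which is 1,000,000 times the printed value.
- If 700 fmol was meant per sample of 50 microlitres: 700 / 0.00005 L = 14,000,000 fmol/L, which is 20,000 times the printed value.

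The per-sample reading is itself an assumption. It shows how far apart the candidate meanings lie.

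**2. Effect of sampling on self-report.** Let T be true adherence, s the probability that an adherent person reports adhering, and f the probability that a non-adherent person does so. All rates are assumed, and the model is per participant. A valid cutoff is one that classifies every sampled person correctly. With unsampled people counted as not adherent, the observed proportion over all participants is T × s.

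- *Under-reporting differs by arm.* T = 0.30 in both arms, s = 0.80 in control and 0.95 in CHC+. Control: 0.30 × 0.80 = 24.0%. CHC+: 0.30 × 0.95 = 28.5%. This is a false benefit of 4.5 percentage points. If s were lower in CHC+, the error would run the other way.
- *Only over-reporting differs by arm.* T = 0.30, s = 0.90 in both arms, f = 0.20 versus 0.40. Both arms give 0.30 × 0.90 = 27%, with no false difference.
- *The same over-reporting, with a cutoff that traces can pass.* Assume that 80% of over-reporters carry some drug and pass. Control: 0.27 + 0.70 × 0.20 × 0.80 = 38.2%. CHC+: 0.27 + 0.70 × 0.40 × 0.80 = 49.4%. This is a false benefit of 11.2 points.
- *Sampling without the self-report condition.* If every adherent person is sampled, s drops out, and a valid cutoff returns 30% in both arms.

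**3. Passages side by side.** The follow-up section makes DBS conditional on reported adherence, while Overall study measures does not. The follow-up section places DBS at 3 and 6 months and the analysis section tests adherence at both, while Table 3 lists biological adherence at 6 months only.

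**The case against.** The strongest reply is that the unit is a print error and not a planned rule. Table 3 contains other stray characters, the unit itself is oddly set, and certified laboratories will run the samples. That is quite possible, but a printed adherence definition still has to be corrected, and the missing governing analyte is not a typographical matter.

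A second reply is that no passage limits the analysis to sampled people, and that the classification of unsampled participants may be fixed in documents not shown. This stands. Counting them as not adherent also removes the false difference when only over-reporting varies by arm. It does not remove it when under-reporting varies, as the 24.0% versus 28.5% case shows.

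A third reply is that DBS is one of several measures. Refills, months on drug and clinic attendance come from medical records, and ART adherence uses viral load or CD4 count. Overall study measures also names initiation and documented HIV status as the primary outcomes. All of this is so. It limits the damage but does not repair the biological row, and the Sample size section does call adherence primary.

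A reader might also infer from the detectable effects, 0.34 for adherence against 0.23 for initiation, that only starters will be analysed, since (0.23/0.34)² = 0.46. The Sample size section defines no effect metric and gives no time point for the 0.23, so these figures support no inferred denominator.

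**Conclusion.** The point holds in two parts.

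- **Cutoff.** The unit is probably wrong, by a factor of 20,000 to 1,000,000 if 700 fmol per sample was meant and the sample holds 1 to 50 microlitres. The governing analyte is not stated.
- **Sampling.** As the follow-up section is written, the biological measure is not independent of self-report. On the assumed rates this alone yields a false difference of 4.5 points with equal true adherence. The size and direction depend on how reporting differs between arms, which the article cannot tell us.

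Three stronger readings go beyond the article. That almost any trace of drug would pass the cutoff needs an assay limit, which is not given. That DBS cannot measure adherence objectively is too strong, because it still refutes false claims of adherence and record-based measures sit beside it. That the randomised comparison is broken by analysing only sampled people or starters assumes an analysis the article does not state.

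**What to change.** 1. Have the assay laboratory confirm the cutoff, and restate it in Table 3 in the unit the laboratory reports, for one named governing analyte.
2. At the planned follow-up visits, collect DBS from every participant with a clinic record or self-report of any PrEP/ART start, whatever adherence they report.
3. State that adherence is analysed over all randomised couples, with non-starters counted as not adherent.
4. Reconcile the follow-up section with Overall study measures on who is sampled, and reconcile the 3- and 6-month collection and analysis with Table 3's single 6-month entry.

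The cost is wording plus a small number of extra DBS cards and assays at visits already planned. The second change is the urgent one: the article describes recruitment as ongoing, and samples not taken cannot be obtained later.

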### Statistical analysis plan and hypotheses

We will examine the distribution, frequency, and missing values in each variable using frequency tables for categorical variables and univariate distributions for continuous variables. We will compare data across the arms to examine the balance of baseline demographic and clinic characteristics using chi-square tests and t-tests or their nonparametric alternatives, as appropriate. Next, we will examine the association between demographics, clinic characteristics, primary outcomes, and any important mediators and moderators to determine which variables will be entered in the generalized linear models (GLM). We will use a GLM with generalized estimating equations (GEE) to test the relative efficacy of the interventions on the primary outcomes. GEE allows one to adjust for clustering and accommodates multiple types of outcomes (dichotomous, continuous, ordinal) and dyadic data analysis. We will use the couple as the unit of analysis for ART/PrEP initiation and adherence. First, we will fit a logit model that regresses the dependent variable on the membership in the arms and visit, and an interaction between visit and arm. Second, if descriptive analysis suggests there are significant differences in demographics or characteristics of clinics across the arms, those variables will be added into the model as covariates. We will test ART/PrEP initiation and adherence across two arms at a time by estimating contrasts at each time point to test both the hypotheses that the CHC+ increases ART/PrEP initiation and adherence. We will use an identical process to estimate the impact of the interventions on AOD use, GBV, sexual risk-taking, communication, and gender norms. The distribution in the GLM will be modified to be multinomial for ordinal outcomes, binary for dichotomous outcomes, and continuous or Poisson for continuous or count outcomes, respectively. The unit of analysis for outcomes (e.g., condomless sex) will be at the couple level and/or individual level, when appropriate, which the study team has done in previous couples-based analyses [15]. Analyses will be performed for the 3-month and 6-month follow-up time periods to determine if there are differential effects over time on ART/PrEP initiation and adherence, and at the 6-month time period for secondary outcomes.

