#### Randomization

To achieve balance in allocation of population groups across the four study arms, stratified randomization by population group (Black African, Coloured, and Mixed) was conducted. A total of 24 catchment areas were selected from the list of 34 catchment areas. The sampling frame included 8 Black African, 8 Coloured and 8 Mixed communities. Within each of the 3 strata, the 8 areas were randomized to the four study arms in a 2:2:2:2 allocation.

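### Covariates for the efficacy model are chosen from the trial's own data (outcome associations and baseline significance tests), while the randomisation stratum is not a stated model term

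*Protocol article*

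**What the plan says.** Four statements in the protocol article matter here; the first three are in the section on the statistical analysis plan and hypotheses.

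- **Outcome-association screen.** Associations with the primary outcomes are looked at first, over a pool of demographic and clinic variables that also takes in "any important mediators and moderators to determine which variables will be entered in the generalized linear models (GLM"). The next sentence there says that a GLM with GEE tests the relative efficacy of the interventions on the primary outcomes.
- **Baseline-difference rule.** Arms are compared at baseline "using chi-square tests and t-tests or their nonparametric alternatives, as appropriate". Then, "if descriptive analysis suggests there are significant differences in demographics or characteristics of clinics across the arms, those variables will be added" to the model.
- **Fixed terms.** Before that second step, "we will fit a logit model that regresses the dependent variable on the membership in the arms and visit, and an interaction" of these two terms. Clustering is mentioned for the efficacy model ("GEE allows one to adjust for clustering"), but not for the baseline tests. The same process is applied to substance use, violence, sexual risk, communication and gender norms.
- **Allocation.** Under Randomization, "stratified randomization by population group (Black African, Coloured, and Mixed) was conducted", with 8 communities per stratum divided 2:2:2:2 among the four arms.

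**The concern.** Three separate issues meet in these rules.

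1. Both selection steps depend on the data. One looks at the outcome. The other uses a significance test, which measures chance imbalance and not prognostic value. Communities were randomised, so a couple-level test with no allowance for clustering rejects too often. The adjusted model would then be settled largely by chance, in a trial with only 24 clusters.
2. The stratum is balanced by design: each arm has 2 communities from each population group. The baseline-difference rule is therefore unlikely to bring it in, and it enters only if the outcome screen happens to select it. When a design balances a prognostic factor and the analysis ignores it, the between-stratum variation stays in the residual and the standard error is too large.
3. Mediators stand in the candidate pool, and no sentence confines them to a separate analysis. Variables that the interventions are meant to change, such as partner communication, gender attitudes and experienced stigma, are measured again at 3 and 6 months (Table 3). Conditioning on one that carries benefit removes part of the total effect.

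**Working it through.** **Inputs from the protocol article.** 24 communities, 20 couples each (Study research design); 3 strata, 2 communities per arm in each (Randomization); ICC 0.05, two-sided 0.05, 80% power, 95% follow-up at 3 months (Sample size). The design counts reproduce: 24 × 20 = 480 couples; 3 × 2 × 20 = 120 per arm.

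**Step 1: false flags from the baseline tests.** Assume couple-level tests that ignore clustering, and let the covariate have the stated ICC.

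- Design effect = 1 + (20 − 1) × ICC = 1 + 19 × 0.05 = 1.95.
- The four-arm chi-square has 3 df and a 5% critical value of 7.815. With the statistic inflated by 1.95, the true rejection rate is P(χ²₃ > 7.815/1.95) = P(χ²₃ > 4.008) = 0.261.
- ICC 0.01: design effect 1.19, P(χ²₃ > 6.567) = 0.087. ICC 0.10: design effect 2.90, P(χ²₃ > 2.695) = 0.441.
- With 10 independent covariates (an assumed number), the chance of at least one false flag is 1 − 0.95¹⁰ = 0.40 if each test is exact, and 1 − (1 − 0.261)¹⁰ = 0.95 if clustering is ignored.

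**Step 2: omitting the stratum.** Let the stratum explain a share s of the between-community variance (an assumption; the article gives no figure). In SD units with 20 × 0.95 = 19 couples per community, the variance of a community mean within stratum is 0.05(1 − s) + 0.95/19 = 0.05(1 − s) + 0.05, and the between-stratum variance is 0.05s. A model with an intercept and the two interventions leaves 21 residual df, and the stratum adds 24 × 0.05s to the residual sum of squares. The standard error is therefore inflated by about √[1 + 24 × 0.05s / (21 × (0.05(1 − s) + 0.05))]:

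- s = 0.25: √(1 + 0.300/1.8375) = 1.08
- s = 0.50: √(1 + 0.600/1.575) = 1.17
- s = 0.75: √(1 + 0.900/1.3125) = 1.30

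A simulation of 40,000 trials of 24 community means used an effect of 0.38 SD, chosen to give about 80% power when s = 0. It is not the protocol's stated 0.23.

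| s | Type I error without stratum | Type I error with stratum | Power without | Power with |
|---|---|---|---|---|
| 0.25 | 3.7% | about 5% | 81% | 85% |
| 0.50 | 2.4% | about 5% | 83% | 90% |
| 0.75 | 1.2% | about 5% | 84% | 94% |

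At s = 0, including the stratum costs about half a percentage point of power.

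A second simulation used the stated type of model: binary couple outcome, GEE logit, robust standard errors. Its control rate (about 35%) and residual community SD (0.25 on the logit scale) are assumed. At stratum SD 0.2 and 0.4, the standard error without the stratum was too large by 4% and 24%, with type I error 4.0% and 1.4%. With the stratum, type I error was about 5%. At SD 0.6 the excess was 56%, but that case implies an ICC near (0.36 + 0.0625)/(0.36 + 0.0625 + 3.29) = 0.11, about twice the protocol's, so it is not relied on. At SD 0 there was no effect. This simulation adds stratum variance on top of a fixed residual, whereas the first holds the total ICC at 0.05, so their power figures are not comparable.

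**Step 3: mediators.** No arithmetic applies. The screening sentence makes mediators candidates for the GLM. The model-building sequence that follows begins with arm, visit and their interaction, and its second step adds only demographic or clinic variables. Adjustment for a mediator is thus neither prescribed nor excluded.

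**The case against.** - **This is a condensed article, and the list of model terms belongs in the SAP.** That would dispose of a bare complaint that the stratum is not listed. But the article states its own selection rules and its own model terms, and those rules are the problem. The stratum matters here because the stated rules give it no reliable way in.
- **Mediators are only candidates.** This stands. A reader might infer that mediators will enter the efficacy model and that the effect estimate is therefore biased toward zero. The text does not support that: the second step admits only demographic and clinic variables, and the screening sentence may also be meant for secondary moderator or mediator models. What remains is an ambiguity that one sentence would close.
- **Omitting the stratum is conservative.** This also stands. A reader might infer from inflated standard errors that the trial's inference is invalid or its effect biased. Type I error falls below 5%, and power in the first simulation stays at or above the planned 80%. The loss is efficiency that the stratified design had already secured.
- **The 26% borrows the outcome ICC for baseline covariates.** True, hence the 9% to 44% range. It covers couple-level variables only; clinic characteristics vary at community level. A falsely flagged baseline covariate does not by itself bias a randomised comparison, and the model fitted first is fixed. The objection narrows the harm to an adjusted model that cannot be known in advance.

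**Conclusion.** The point holds as a should-fix. The covariate rules are data-dependent, and under couple-level tests that ignore clustering the baseline screen would flag a balanced variable about 26% of the time at the protocol's ICC (9% to 44% for ICC 0.01 to 0.10). That the tests ignore clustering is an inference from the article's silence, not something it states.

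Leaving out the stratum makes the test conservative: standard errors are about 8% to 30% too large, and power is roughly 4 to 10 percentage points lower than it could be, if the stratum explains 25% to 75% of between-community variance. That share is assumed; if it is zero, nothing is lost. There is no bias under the null from this source.

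Adjustment for post-randomisation mediators is permitted but not required. If it were done, it would attenuate the total effect where the mediator carries benefit, by an amount that cannot be computed from the document.

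**What to change.** Replace both selection steps with a prespecified efficacy model:

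- Terms: arm, visit, arm × visit and population-group stratum (3 levels).
- A short fixed list of baseline covariates. Couple HIV status at screening is one option, not a necessity. Another is the baseline value of the outcome, where baseline is not already modelled as a visit.
- A sentence stating that mediators and other post-randomisation variables are excluded from efficacy models and analysed only in a separate mediation analysis.
- Baseline balance reported descriptively, with no significance test driving the model.

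Because the article applies the same process to the secondary outcomes, one change covers those too. The stratum is already known and HIV status is already tested at screening, so no new data are needed. The cost is a change of wording and 2 cluster-level degrees of freedom (21 to 19 in the model used above), which is about half a point of power if the stratum proves uninformative. It should be settled before outcome data are analysed by arm.
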